**Table 3.5: Proposed data analysis table**

| **Descriptive Statistics** | **Categorical data** | **Numerical data** | |
| --- | --- | --- | --- |
|  |  | **Normally distributed** | **Non-normally distributed** |
| ***Socio demographic information***   - Age - Gender   ***Anthropometric measures***   - Weight, height, MUAC - Categorization according to Z-scores: height for age, weight for age and BMI for age   ***Nutrient intake from 24hr recall***   - Total intake, - Consumption pattern   ***Dietary patterns***  Frequency of inclusion of food item in the FFQ  Morbidity diary  **Biochemical measures**   - Serum zinc - haemoglobin - Serum Ferritin - C-reactive protein - Transferrin saturation - Serum ferritin | Frequencies n (%) | Mean $\pm$ SD | Median and IQR |
| ***Analytical statistics-*** |  |  |  |
| ***Comparison of micronutrient status by subject characteristics*** | Pearson’s Chi-square test/Fishers exact test | ANOVA/T-test | Kruskal-Wallis/Mann-Whitney U tests |
| ***Association between dietary intakes and micronutrient status*** | Regression analyses with dietary intakes and anthropometric indices as dependent variables and all other as independent | | |
| ***Validation of dietary intake and micronutrient status against the intervention*** | Spearman’s correlation coefficient  Comparison of means/means Weighted kappa statistic for agreement testing  Bland Altman plots for bias and agreement testing | | |

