***Figure 4: MUAC measuring tape.***

The MUAC is the circumference of the left upper arm that is measured at the mid-point between the tips of the shoulder and elbow. The participant’s left arm will be bent then the researcher will find and mark the mid-point between the two marks. There arm will be hanging straight down, and a MUAC tape will be wrapped around the arm at the midpoint mark. The MUAC will be measured to the nearest 1m (**see Appendix B**) for recording.

1. ***Dietary intake and patterns***

A one day 24-hour recall will be used to collect detailed information about all foods and beverages consumed using the multiple pass method (Steinfeldt *et al*., 2013). Foods will have been consumed in the past 24 hours, most commonly, from midnight to midnight the previous day (**see Appendix C)**. Six daily intervals will be included, namely: breakfast (period up to 09h00), In-between snack (between 09h00 and 12h00), lunch (12h00 to 14h00), In-between snack (14h00 to 18h00), dinner (18h00 to 20h00), and after dinner (after 20h00). Guardian/parents will provide this information. A FFQ will be used to establish food consumption patterns including the *Cucurbita moschata* seeds. A selected pictorial FFQ will be designed for the children to establish if they know and consume the seeds (**see Appendix D**). Preschool menu will also be evaluated at this stage using the 24 hr recall form for recording at least once a week during the implementation of the intervention.

1. ***Biochemical measurements***

Zinc status will be determined by serum zinc concentrations and iron status via haemoglobin, serum ferritin, transferrin receptor and C- reactive protein (CRP) among pre-school children using flame atomic absorption spectrophotometer. The anthropometric status of the preschool children will be assessed by measuring weight and height to calculate the body mass index (BMI).

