***Dietary patterns***

The 24-hour recall will be analysed using the 11-food item to determine dietary diversity score. The FFQ will be analysed using SPSS version 23 for frequencies as daily, weekly, monthly, seasonal or never. Consumption of indigenous foods will be determined using frequencies. Food finder (MRC) will also be used to analyse the nutrient intakes.

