**APPENDIX C: 24-hour recall**

| **Section: Dietary Patterns and Intakes of children** |
| --- |

**Please describe the foods (meals and snacks) that you ate yesterday during the day and night, whether at home or outside the home. Start with the first food eaten in the morning**

*Write down all food and drinks mentioned by the respondent. When the respondent has finished probe for meals and snacks not mentioned*

| **Meal** | **Time of meal** | **Food item description** |
| --- | --- | --- |
| **Breakfast** |  |  |
| **Snack** |  |  |
| **Lunch** |  |  |
| **Snack** |  |  |
| **Dinner** |  |  |
| **Snack** |  |  |

**[Household level: consider foods eaten by the child, and exclude foods purchased and eaten outside of the home or at the preschool]**

*When the respondent recall is complete, fill in the food groups based on the information recorded above. For any food groups not mentioned, ask the respondent if a food item from this group was consumed.*

| Question  number | Food group | Examples | Yes = 1  No = 0 |
| --- | --- | --- | --- |
|  | CEREALS | corn/maize, rice, wheat, sorghum, millet or any other grains or foods made from these (e.g. bread, noodles, porridge or other grain products) + *insert local foods e.g.* *ugali, nshima, porridge or pastes or other locally* *available grains* |  |
|  | VITAMIN A RICH VEGETABLES AND TUBERS | pumpkin, carrots, squash, or sweet potatoes that are orange inside + *other locally available vitamin-A rich* *vegetables (e.g. red sweet pepper)* |  |
|  | WHITE TUBERS AND ROOTS | white potatoes, white yams, white cassava, or other foods made from roots |  |
|  | DARK GREEN LEAFY VEGETABLES | dark green/leafy vegetables, including wild ones + *locally available vitamin-A rich leaves such as amaranth, cassava leaves, kale, spinach etc.* |  |
|  | OTHER VEGETABLES | other vegetables (e.g. tomato, onion, eggplant),  including wild vegetables |  |
|  | VITAMIN A RICH FRUITS | ripe mangoes, cantaloupe, apricots (fresh or dried), ripe papaya, dried peaches + *other locally available vitamin* *A-rich fruits* |  |
|  | OTHER FRUITS | other fruits, including wild fruits |  |
|  | ORGAN MEAT (IRON RICH) | liver, kidney, heart or other organ meats or blood-based foods |  |
|  | FLESH MEATS | beef, pork, lamb, goat, rabbit, wild game, chicken, duck, or other birds |  |
|  | EGGS | chicken, duck, guinea hen or any other egg |  |
|  | FISH | fresh or dried fish or shellfish |  |

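### Total nutrient intake is planned from a 24-hour recall form that records no amounts and is told to leave out preschool food

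*Protocol*

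**What the plan says.** The protocol commits to nutrient quantities as well as food patterns.

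- Table 3.5 lists "Nutrient intake from 24hr recall", with total intake beneath it, to be summarised by mean and SD or by median and IQR. A later row plans regressions for "Association between dietary intakes and micronutrient status".
- Section 3.6.2.5, data analysis, Dietary patterns: "Food finder (MRC) will also be used to analyse the nutrient intakes".
- Section 3.11 gives Chapter six to consumption of the seeds and what they contribute to nutrient intake.
- Section 3.6.4.4 repeats the baseline measurements and procedures after the feeding period.

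The procedure in Section 3.6.2.5 (Dietary intake and patterns) reads: "A one day 24-hour recall will be used to collect detailed information about all foods and beverages consumed using the multiple pass method". It names no portion-size aid or household measure.

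The recall form, Appendix C, has three columns: meal, time of meal and "Food item description". The interviewer is told: "Write down all food and drinks mentioned by the respondent", and then to probe for missed meals and snacks. A yes/no list of food groups follows. A bracketed household-level note tells the interviewer to "exclude foods purchased and eaten outside of the home or at the preschool".

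**The concern.** A food-composition program needs a food and an amount. The form supplies only the food. A later analysis plan cannot recover a quantity that was never written down, so the gap has to be closed before the baseline survey.

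The bracketed note causes a second problem. Section 3.6.3.4 has the study dish served with lunch at the preschool. If the note is followed, the recall leaves out that lunch and anything else eaten there, and what remains is not a total.

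At stake are three secondary products: the description of iron and zinc intake, any Table 3.5 analysis that uses nutrient intake, and the total-diet denominator for the seeds' contribution in Chapter six.

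**Working it through.** No sample size, power or error-rate figure is involved, and the plan states no intake figure to reproduce. The check compares what the analysis needs with what each form collects.

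**What the analysis needs.** For child *i* and nutrient *k*:

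intake(i,k) = sum over foods *f* of [ amount(i,f) in g × content(f,k) per 100 g ÷ 100 ]

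**What each form supplies.**

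| Form | Amount eaten? | Planned use | Needs amounts? |
| --- | --- | --- | --- |
| Appendix C, 24-hour recall | No | Diversity score | No |
| Appendix C, 24-hour recall | No | Total nutrient intake (Table 3.5) | Yes |
| Appendix D, FFQ | No, frequency only | Frequencies | No |
| Appendix F, food diary | No | Frequencies (Section 3.6.3.6) | No |
| Appendix E, plate waste | Yes, grams served and wasted | Adherence to the study dish | Yes, and has them |

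The mismatch is therefore confined to one form and one use: Appendix C as the source of total nutrient intake.

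**Can Appendix E fill the gap?** No. It covers the study dish only, and Section 3.6.3.5 applies it to ten randomly selected children each time, twice a week, during the feeding phase. If the ten are drawn within one preschool of the estimated 73 children in the feeding-trial schematic, that is 10 ÷ 73 = 14% per session. Repeated sampling over six months could describe intake of the dish well, but it says nothing about the rest of the diet. It also does not belong to the recall day.

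**Can the preschool menu fill the gap?** No. The protocol says: "Preschool menu will also be evaluated at this stage using the 24 hr recall form for recording". That form has no amount field, and a menu describes what was offered, not what each child ate.

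**What follows if the plan is carried out as written.** With a default portion p(f) in place of the amount, the formula becomes:

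intake*(i,k) = sum over *f* of [ times mentioned(i,f) × p(f) × content(f,k) ÷ 100 ]

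Two children who name the same foods the same number of times receive the same intake, whatever each ate. Differences in which foods were eaten, and how often, survive. Differences in quantity do not.

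**Is the scope of the recall clear?** No. The opening prompt of Appendix C asks for food eaten both in and outside the home. The bracketed note then excludes food bought and eaten outside the home or at the preschool, and a later item asks separately about eating outside the home. The note is labelled as household level yet speaks of what the child ate. The form does not say which instruction governs a child's nutrient intake.

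**The case against.** The best defence is that the instrument is not final and the procedure may already imply amounts. The multiple pass method is named, detailed information is promised, and the description column is free text. The fieldworkers are nutritionists whose methods are to be standardised during piloting, and the record sheet is to be pilot tested. Amounts could therefore be written down in practice. That stands as a possibility. However, nothing in the protocol asks for amounts, and nothing would make the practice uniform across fieldworkers, preschools or the two surveys.

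A second defence is reach. The stated objective for the recall is a dietary diversity score, and the FFQ objective is dietary patterns. Neither needs amounts, and the primary aim rests on blood measurements. This stands in full and limits the importance of the point.

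Three stronger readings are tempting, and the documents do not support them.

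- *A reader might infer that no form records any quantity, so that the seeds' contribution has no basis.* Appendix E records grams of the study dish, Section 3.6.3.4 gives a provisional serving of 64 g, and phase one plans nutrient analysis of the recipes. The seed part has quantities behind it. The total-diet denominator does not.
- *A reader might infer that the planned regressions are attenuated.* Table 3.5 makes dietary intake a dependent variable. Classical error there costs precision and does not shrink the slope. What can be said is that any association running through the quantity eaten would be missed.
- *A reader might infer a specific error factor from assumed portions.* For a single food the content cancels, so the ratio of two computed intakes is just the ratio of the two portions assumed. Such an example says nothing about the error in a child's total.

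**Conclusion.** The point holds for Appendix C set against Table 3.5 and the Food finder sentence. As written, total iron and zinc intake could be obtained only by imputing portions that the protocol does not specify. The result would carry no between-child variation in quantity and, if the bracketed note is followed, would omit preschool meals. Default portions would still weight foods by their iron and zinc content and reflect how often they were eaten, so the figures would be degraded rather than empty.

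The size cannot be expressed as a number from the documents. Its extent can be stated: it affects recall-based nutrient intake, any Table 3.5 analysis that uses it, and the denominator of the Chapter six contribution. It leaves untouched the diversity score, the FFQ and diary frequencies, and the comparison of serum zinc and iron status between groups. The conclusion assumes that Appendix C is used as printed and that amounts are not added informally. It should be corrected before data collection, but it does not threaten the primary aim.

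**What to change.** Preferred change: add a column to Appendix C for the amount eaten, in household measures or grams, and name in Section 3.6.2.5 the cups, spoons and bowls to be shown to caregivers. Use the same form and measures at baseline and after the feeding period. Reconcile the bracketed exclusion with the opening prompt so that preschool food counts towards the child's intake. Because caregivers answer the recall, state who supplies the preschool amounts. The cost is a few more minutes per interview and an arrangement for the preschool meal. The amount column alone would not be enough, since the total would still omit preschool food.

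Alternative: delete total intake from Table 3.5 and remove the Food finder sentence. Limit the Chapter six claim to what the study dish supplies, and report diversity and frequency only. This costs a few lines of text and gives up the nutrient-intake results.

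Appendices D and F need no change for their planned frequency analyses. Neither option alters the design, the sample or the conduct of the feeding trial.

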**2.3. Main aim of the study**

The primary aim of this study is to test the efficacy of consumption of *Cucurbita moschata* (Butternut) seeds in improving zinc and iron status in preschool children in the Vhembe district, Limpopo province of South Africa, and the secondary aim is to describe the nutritional, zinc and iron status of the children. To attain the aims of this study the following objectives have been developed. Objectives of this study are outlined in each phase

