**2.5. Expected outcomes**

- Zinc and iron status of the intervention group will improve from baseline levels after consumption of the seeds for 6 months.
- Eating patterns of the participants will improve because of the nutrition education.
- Consumption of fruits and vegetables will increase because of the nutrition education.

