**Visit 3 and 4**

Arrangements for data collection will be made with the pre-school management. A full day or two will be required for each preschool and space for data collection will be requested form the preschool management.

The baseline survey will thus require four visits per preschool (visit 1: 2 days; visit 2: 6 days; visit 3 and 4: 12 days) for a total of 20 days.

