***Blood collection***

The children will be given single-dose of albendazole (400 mg) or mebendazole (500 mg) for deworming at this phase. A phlebotomist will collect 5ml blood samples from the participants. The participant’s skin will be cleaned with cotton wool and 70% alcohol at the site of the antecubital vein and the participants’ arm will be restricted with a tourniquet for < 1 minute. A trace element-free, siliconized 23-G needle will be inserted into an antecubital vein, and 5ml blood drawn into two trace element-free evacuated tubes. These will be centrifuged at room temperature for 10 min at 2000 × g and divided into aliquots to separate serum from the blood at the preschool site. Serum will be transferred into new tubes for storage in a cooler box with crushed ice prior to being frozen at −20°C until further analysed. Analysis will be conducted subsequently at Ampath laboratories in Polokwane, South Africa. routine quality control measures will be employed.

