31. Has the child completed all immunisations?

| Yes | No |
| --- | --- |

Comment ………………………………………………………………………………..

32 Blood sample taken:

| Yes | No |
| --- | --- |

- 1. Time of blood collection………………………………
  2. Time of the previous meal……………………………

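### Table 3.5 does not carry out the between-arm comparison of zinc and iron that Section 3.6.4.4 announces, and Section 2.5 words success as a change within one arm

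*Protocol*

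**What the plan says.** Section 2.3 of the protocol sets the primary aim as the efficacy of consuming the "seeds in improving zinc and iron status in preschool children". Four places then bear on how that is judged.

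- Section 3.6.4.4 keeps the baseline methods and adds regression and ANOVA, both for change over time and for the contrast of the two arms. It names no marker and sends the reader to Table 3.5.
- Table 3.5 has three analytical rows. The first compares micronutrient status across subject characteristics. The second, headed as an association of intake with micronutrient status, specifies "Regression analyses with dietary intakes and anthropometric indices as dependent variables and all other as independent". The third is "Validation of dietary intake and micronutrient status against the intervention"; it lists Spearman correlation, a comparison of means, weighted kappa and "Bland Altman plots for bias and agreement testing".
- Section 2.5 states the expected result as "Zinc and iron status of the intervention group will improve from baseline levels after consumption of the seeds for 6 months".
- Section 3.11 describes the efficacy chapter (chapter seven) as a comparison of the two groups on zinc and iron change over six months.

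Under Blood collection, in the baseline phase: "The children will be given single-dose of albendazole (400 mg) or mebendazole (500 mg) for deworming at this phase". No distinction is made by arm.

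**The concern.** The table is where an analyst will look for the method, and it does not match the aim or the text that introduces it. A regression with diet and anthropometry on the left cannot return a seed effect on zinc or iron. Kappa and Bland-Altman compare two measurements of one quantity, and allocation to an arm is not a measurement of zinc. Section 2.5 leaves out the control group.

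Text, table and expected outcome thus give three different bases for judging efficacy, and the choice could be made after the data are seen. The timetable makes this practical: Section 3.12 puts post-intervention collection in November 2021 and the statistician's consultation on analysis in January 2022. At worst, a rise in the intervention group that the control group shares would be reported as an effect of the seeds.

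**Working it through.** **1. The rows set against the aim.**

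| Table 3.5 row | Outcome side | Contrast | Arm effect on zinc or iron? |
| --- | --- | --- | --- |
| Comparison | Micronutrient status | Subject characteristics | No, arm not named |
| Association (regression) | Diet, anthropometry | All other variables | No, zinc and iron are predictors |
| Validation | Diet and micronutrient status | The intervention | Not by kappa or Bland-Altman; the comparison of means names neither groups nor marker |

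Section 3.6.4.4 does name the arm contrast, but no row specifies it.

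**2. Direction of the regression.** Illustration on assumed values: 200,000 simulated children, arm raises zinc by 0.30 SD, diet unrelated to both.

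- Diet regressed on arm and zinc: arm coefficient 0.004.
- Zinc regressed on arm: arm coefficient 0.299.

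This follows from the structure. The arm coefficient in a diet model describes diet.

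**3. Within-arm change as evidence.** The arm size comes from Section 3.4. Its formula reproduces: 40291/(1 + 40291 × 0.05²) = 40291/101.7275 = 396.07, so 396; 396 × 1.10 = 435.6, so 436. (One printed line omits the square, but the printed denominator uses it.) An equal split, assumed here, gives 396/2 = 198 per arm.

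Let the seeds do nothing and let both arms shift by s (in SD) between visits, with pre-post correlation r. The within-arm change has SE = √(2(1 − r)/198), and the chance of a two-sided p < 0.05 is Φ(s/SE − 1.96) + Φ(−s/SE − 1.96).

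- r = 0.5: SE = √(1/198) = 0.071. For s = 0.1, 0.2, 0.3 the chance is 29%, 80%, 99%.
- r = 0.7: SE = √(0.6/198) = 0.055. The chance is 44%, 95%, 100%.

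Both s and r are assumptions, and children are treated as independent. A shared shift is plausible on the protocol's own account: Section 1.9 links worm infection to iron loss and anaemia, and deworming is given at baseline. The between-arm contrast removes a shift common to both arms.

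**4. Why the new row must carry the preschool.** Section 3.6.3.3 randomises preschools, and the tests named are child-level. With about 73 children per preschool (feeding-trial schematic, Section 3.6.3) the design effect is 1 + 72 × ICC. For assumed ICCs of 0.01, 0.05 and 0.10 it is 1.72, 4.60 and 8.20. By 2(1 − Φ(1.96/√DE)), a nominal 5% child-level test then rejects a true null 13.5%, 36.1% and 49.4% of the time. No ICC is given in the protocol.

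**5. Gain from baseline adjustment.** For child-level variance, change-score over ANCOVA is 2(1 − r)/(1 − r²) = 2/(1 + r): 1.54, 1.33 and 1.18 at assumed r of 0.3, 0.5 and 0.7. It does not apply to variance between preschools.

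**The case against.** A reader might infer that the protocol names no analysis able to estimate the seed effect. The documents do not support that. Section 3.6.4.4 names regression and ANOVA between the arms, Section 3.11 plans a between-group efficacy chapter, and Section 3.6.3.3 describes a controlled design whose purpose is comparison with control. Micronutrient status is the outcome in the first analytical row, and the validation row also lists a comparison of means. The regression row can be read as serving the secondary, descriptive aim, and Section 2.5 is a list of expectations, not a formal success criterion. All of this stands and limits the point to a mismatch.

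Two further inferences also go too far.

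- That the plan throws away a known share of information by analysing change scores. Section 3.6.4.4 does not fix a change-score model, since its regression could adjust for baseline, and r is assumed.
- That time of draw biases the zinc comparison by a definite amount, because Table 3.2 gives cut-offs of 65 and 57 μg/dL for morning and afternoon. A gap between cut-offs is not a shift in means, and no imbalance between arms is documented. The statement "A full day or two will be required for each preschool" covers all data collection, not blood draws alone.

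What the objection does not remove: Section 3.6.4.4 refers to Table 3.5 for the method, and the table contains no arm contrast on any zinc or iron marker.

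**Conclusion.** The point holds as an inconsistency in how the primary aim is to be judged. The text announces a between-arm comparison. The table it cites reverses the regression, applies agreement statistics to the intervention, and compares micronutrient status by characteristics other than arm. Section 2.5 describes a result that needs no control group.

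This rests on reading the passages together and needs no assumed figure. The 29% to 99% range and the design effects only illustrate what is at stake, under the stated assumptions. They do not predict this trial's results. It does not follow that a between-arm analysis is absent or that reported results would be wrong; the efficacy analysis is left open where it should be fixed.

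The between-arm contrast would estimate seed paste plus song against mashed flesh, because Section 3.6.3 gives the song to the experimental group only.

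**What to change.** Add one efficacy row to Table 3.5 for serum zinc and for each named iron marker: haemoglobin, ferritin on the log scale, and whichever transferrin measure the protocol settles on (the objectives name the receptor, Table 3.5 names saturation). In each:

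- the six-month value is the dependent variable, arm is the effect, and the child's baseline value is a covariate;
- preschool is treated as the randomised cluster, with a small-sample method suited to six to eight clusters, such as analysis of cluster-level summaries or a degrees-of-freedom correction.

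Delete kappa and Bland-Altman for the intervention. Keep the diet and anthropometry regression only as a secondary association analysis. Reword Section 2.5 so that efficacy is the between-arm difference, labelled as seed paste plus song versus control, and within-arm change is descriptive.

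Adjustment for CRP and for draw and meal time may be added as a supportive analysis. The Appendix B record sheet already has "Time of blood collection" and the time of the previous meal.

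The cost is wording and slightly more analysis work, using data already planned. Intervals will be wider because clustering is respected: at the assumed ICCs above, the standard error grows by √1.72 = 1.31 to √8.20 = 2.86 before any gain from baseline adjustment. The change should be made before outcome data are seen.
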